**Blinding**

It is impossible to blind the participants and TCC coaches in this trial. Nevertheless, we will assign a specified project manager to be in charge of the random allocated sequence and blind code of allocation in which TCC training group or control group will be replaced by the alphabet A or B. In addition, we will define each investigators a well-defined obligation; the project manager and TCC coaches will be not take part in the assessment of outcome; the outcome assessors and the statistic analyzer will be not involve in the participants’ recruitment and allocating. The allocation sequence and blind codes will be preserved hold by an independent project manager until the statistic analysis is completed.

**Intervention**

**TCC training group**

Participants allocated to the TCC training groups will receive 12 weeks of TCC training. The TCC training will be instructed by two experienced TCC coaches, who have been qualified and engaged in the teaching of TCC course for at least 15 years. The 24 forms simplified TCC, which is recommended as the popularity health sport by General Administration of Sport of China, will be applied to members of the intervention group. Participants of TCC training group will be gathered to exercise at the campus gymnasium together. TCC training will be performed for 60 minutes per time and also include 10 minutes of warm-up (e.g., weight shifting, arm swinging, gentle stretches of the neck) at a frequency of five days a week. Participants will be taught the “meditation through movement” art of TCC, which includes the rationale states of TCC constitute, action essence of TCC, the TCM philosophy opinion of TCC, and deep breathing method. The instruction of TCC will be both verbal and visual. The systematic approach has been designed by two coaches and can be viewed on DVD.

**Control group**

No specific exercise will be administered on the participants in control group. They will be informed to maintain their original lifestyle.

**Intervention regimen**

The intervention period in this trial will last 12 weeks. All participants will be required to record physical activity diaries including the type and intensity of physical activity or exercises, as well as the sedentary time, sleeping time everyday throughout this study.

**Follow-up period**

During the 12-week follow-up period, all of the participants will return to their original lifestyles, but be required to record their daily physical activities or sport information. The primary outcomes will be re-measured at end of follow-up period.

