**Statistical analyses plan**

SPSS21.0 statistical analysis software will be used to analyze data. The primary outcomes of participants who are randomized and received at least one treatment week will be carried by the intention-to-treat (ITT) analysis. Per-protocol subjects analysis（PPS）of the primary outcomes will include participants who have completed the 24-week study without major protocol violations and have compliance rate > 85%. We will compare the results of the ITT with that PP analysis to check-up whether the results are consistent or not. The continuous variables will be expressed using means with standard deviations or medians with ranges. For the variables with a normal distribution, statistical comparisons between the groups will be made by using a *t* test. If the variables have a non-normal distribution of ordinal level, statistical comparison between groups will be made using the Mann-Whitney *U* test. Measures with a discrete distribution will be expressed as percentages and analyzed by theχ2 or Fisher’s exact test as appropriate. A general linear model or Logistic regression model will be applied to adjust the confounding influence if necessary. The *p* value is less than or equal to 0.05 will be considered as a test by the difference has statistical significance.

Participants’ recruitment

Eligible patients n=206

Baseline assessment

Exclusion (reasons): n=

Not meeting inclusion criteria: n=

Declined to participate: n=

Other reasons: n=

Randomization allocation

TCC training group

n=103

Control group

n=103

Drop out (reasons): n=

TCC training group: n=

Control group: n=

Outcome assessment after intervention: balance ability, lower limbs proprioception, flexibility, physical fitness, self-efficiency, psychological symptoms ,attention, stress, self-esteem, mood and mindfulness, quality of life, quality of sleep, safety outcomes.

Follow up for 12 weeks

Lost to follow up: n=

TCC training group: n=

Control group: n=

Outcome assessment after follow-up period

Included analysis: n=

TCC training group: n=

Control group: n=

Statistic analysis

Excluded from analysis: n=

TCC training group: n=

Control group: n=

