**Recruitment**

**Allocation and intervention**

**Follow up**

**Analysis**

**Figure 1 Flow diagram of participants**

| **Table 1 Trial Processes Chart**   | Items | Before enrollment (week) | TCC training phase(week) | Training end (week) | Follow-up (week) | Follow-up end(week) | | --- | --- | --- | --- | --- | --- | | **-2-(-1)** | **1-12** | **13** | **13-24** | **25** | | Inclusion criteria | * |  |  |  |  | | Exclusion criteria | * |  |  |  |  | | Informed consent | * |  |  |  |  | | Baseline | * |  |  |  |  | | Randomization | * |  |  |  |  | | Self-esteem | * |  | * |  | * | | Mood and mindfulness | * |  | * |  | * | | Self-efficiency | * |  | * |  | * | | Psychological symptom score | * |  | * |  | * | | Stress test | * |  | * |  | * | | Flexibility | * |  | * |  | * | | Step testing | * |  | * |  | * | | Rest heart rate | * |  | * |  | * | | Vital Capacity | * |  | * |  | * | | Systolic [blood](app:ds:blood) [pressure](app:ds:pressure) | * |  | * |  | * | | [Diastolic](app:ds:diastolic) [blood](app:ds:blood) [pressure](app:ds:pressure) | * |  | * |  | * | | Balance | * |  | * |  | * | | [Lower](app:ds:lower) [limbs](app:ds:limbs) proprioception | * |  | * |  | * | | Attention span | * |  | * |  | * | | Quality of life | * |  | * |  | * | | Quality of sleep | * |  | * |  | * | | Safety outcomes |  | * |  | * |  | | Self-report diaries |  | * |  | * |  | |
| --- | --- | --- | --- | --- | --- | --- | --- | --- | --- | --- | --- | --- | --- | --- | --- | --- | --- | --- | --- | --- | --- | --- | --- | --- | --- | --- | --- | --- | --- | --- | --- | --- | --- | --- | --- | --- | --- | --- | --- | --- | --- | --- | --- | --- | --- | --- | --- | --- | --- | --- | --- | --- | --- | --- | --- | --- | --- | --- | --- | --- | --- | --- | --- | --- | --- | --- | --- | --- | --- | --- | --- | --- | --- | --- | --- | --- | --- | --- | --- | --- | --- | --- | --- | --- | --- | --- | --- | --- | --- | --- | --- | --- | --- | --- | --- | --- | --- | --- | --- | --- | --- | --- | --- | --- | --- | --- | --- | --- | --- | --- | --- | --- | --- | --- | --- | --- | --- | --- | --- | --- | --- | --- | --- | --- | --- | --- | --- | --- | --- | --- | --- | --- | --- | --- | --- | --- | --- | --- | --- | --- | --- | --- | --- | --- | --- | --- | --- | --- | --- |

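### The rule that withdraws students for practising TCC names controls only and has no time limit, so the week-25 comparison can lose TCC practisers from one arm alone

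*Protocol*

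**What the plan says.** The Protocol's Follow-up period section describes the 12 weeks after training in one sentence for both arms: "all of the participants will return to their original lifestyles, but be required to record their daily physical activities or sport information". It then adds: "The primary outcomes will be re-measured at end of follow-up period". Table 1 places that assessment at week 25.

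The only rule on practising TCC after randomisation is item 5 of the withdrawal criteria. It names the control group, applies to regular TCC practice and gives no time window. The list has no item for a student in the TCC arm who goes on practising once the course has ended.

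The Statistical analyses plan section defines two sets. For the first: "The primary outcomes of participants who are randomized and received at least one treatment week will be carried by the intention-to-treat (ITT) analysis". The per-protocol set holds "participants who have completed the 24-week study without major protocol violations and have compliance rate > 85" per cent. What counts as a major violation is not defined. Activity diaries are kept by both arms throughout ("All participants will be required to record physical activity diaries including the type and intensity of physical activity or exercises"), and Table 1 schedules them for weeks 1-12 and 13-24.

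**The concern.** The exclusion criteria keep out long-term TCC practitioners, so for an eligible student a return to previous habits means a return to no long-term TCC practice. Regular TCC in weeks 13-24 therefore departs from the Follow-up period section in either arm. The stated consequence differs by arm: a control is withdrawn, while for a trained student nothing is said.

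A withdrawal rule triggered by behaviour after randomisation, and applied to one arm, undoes part of what randomisation provides. Controls who take up TCC are unlikely to be a random sample of controls. If their week-25 data are lost, the remaining controls are a selected group compared with a TCC arm that was not selected in the same way. The result then has no clear meaning. It is not the effect of assignment, because some assigned controls are missing for a reason tied to their behaviour. It is not a comparison off TCC either, because trained students who still practise remain.

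**Working it through.** No figure in the Protocol depends on this point, so the main check sets the rules side by side for two students who do the same thing in the follow-up phase.

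| Rule | Control who takes up regular TCC in week 15 | Trained student who continues regular TCC to week 24 |
| --- | --- | --- |
| Follow-up period section | Departs from it | Departs from it |
| Withdrawal item 5 | Withdrawn, since no time limit is set | Not covered |
| Week-25 measurement | Not provided for after withdrawal | Scheduled |
| Intention-to-treat set | Not expressly removed, but may have no week-25 value | In, with a week-25 value |
| Per-protocol set | Out, since the 24-week study is not completed | Open, since major violations are undefined |

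The asymmetry comes from withdrawal item 5 and carries into the analysis through missing week-25 data and through the 24-week completion requirement.

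**Inputs for a rough size.** From Sample size estimation: mean 531.25, SD 173.78, expected improvement 15%, 93 per group. Balance is used because it is the only outcome with figures.

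- Planned effect: 0.15 × 531.25 = 79.69 units.
- Standard error of a difference with 93 per group: 173.78 × √(2/93) = 25.5 units.

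**Dropping controls.** Let g be the share of controls dropped under item 5 and D the week-25 difference between the controls who stay and those who are dropped. The full control mean is (1 − g) × mean(stay) + g × mean(dropped), so leaving out the dropped students moves the control mean by g × D. Neither g nor D is in the Protocol. With D assumed equal to 79.69:

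- g = 5%: 0.05 × 79.69 = 4.0 units, 0.16 SE
- g = 10%: 0.10 × 79.69 = 8.0 units, 0.31 SE
- g = 20%: 0.20 × 79.69 = 15.9 units, 0.63 SE

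**Continued practice in the trained arm.** Let f be the share who continue. Assume that those who stop keep no effect, those who continue keep all of it, and no control takes up TCC. The week-25 difference is then f × 79.69:

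- f = 25%: 19.9 units; power 12% (two-sided 0.05, 93 per group)
- f = 50%: 39.8 units, which is 39.8 / 25.5 = 1.56 SE; power 35%
- f = 75%: 59.8 units; power 65%
- f = 100%: 79.7 units; power 88%

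This second set shows only that a week-25 difference can arise with no carry-over at all. It is an argument about how the result should be described and does not show that the comparison is biased.

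**The case against.** The strongest reply is that the week-25 comparison is sound as planned. Randomised groups compared at week 25 estimate the effect of being assigned the course, including any practice that it prompts. The Protocol's objective is the effectiveness of TCC, and no section names persistence after stopping as an aim. This largely stands. A reader might infer that the follow-up phase exists to show a lasting effect and that it fails to do so. The documents do not support that, because the aim is not stated. The reply does depend on controls being kept and measured, however, and item 5 works against this.

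A reader might also infer three further things that the documents do not establish:

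- **The diaries are collected and never used.** The analysis section gives them no role, but tabulating them and planning supportive analyses are matters that a statistical analysis plan may cover, and that plan is not at hand.
- **Trained students who continue stay in the per-protocol set.** This cannot be said while major violations are undefined; continued TCC could be classed as one.
- **Home practice is likely because of the DVD.** The text says "The systematic approach has been designed by two coaches and can be viewed on DVD", but not that students receive a copy. It is weak support.

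It is also fair to object that the intention-to-treat definition does not expressly remove withdrawn students, so the loss of controls is possible rather than certain. That stands, and the conclusion is worded accordingly. Finally, the shares used in the working are assumptions, and the shifts from dropping controls are below one standard error. That stands too.

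**Conclusion.** The point holds in a limited form. Withdrawal item 5 treats the same behaviour in weeks 13-24 differently by arm, and it conflicts with a Follow-up period section that describes one expectation for everyone. Followed as written, it can remove TCC practisers from the control arm only, which leaves the week-25 comparison without a clear meaning.

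The size cannot be fixed from the Protocol. Under the stated assumptions the distortion from dropping 5% to 20% of controls is 4.0 to 15.9 units on balance, or 0.16 to 0.63 standard errors; the direction and size in practice depend on who takes up TCC. The 12-week comparison, on which the sample size rests, is not affected by practice in weeks 13-24.

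It does not follow that the follow-up phase is uninformative. With controls retained, week 25 gives a valid randomised estimate of the effect of assignment to the course. It should not be reported as an effect that persists after practice stops. Adjusting for diary data would not turn it into one, because continued practice is self-selected after randomisation.

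**What to change.** Reconcile the Withdrawal criteria, Follow-up period and Statistical analyses plan sections:

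1. Change item 5 so that a control who takes up regular TCC is recorded as deviating from the plan but is still measured at the scheduled assessments and analysed by intention to treat in the control group.
2. State that the week-25 comparison is the effect of assignment to a 12-week TCC course, whatever is practised afterwards, and do not describe it as persistence after practice stops.
3. If TCC practice in weeks 13-24 is a reason for exclusion from the per-protocol set, apply it alike in both arms.

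The cost is wording; the assessments are already scheduled. There are two small downsides. Keeping controls who start TCC may dilute the difference slightly: if 10% did so and gained the full planned effect, by 0.10 × 79.69 = 8.0 units. The claim about lasting effect also becomes more modest.

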**Outcomes measurement**

The primary or secondary outcomes will be tested at baseline, 12 and 24 week post-intervention. A schedule of assessments that will be carried out is listed in Table 1. The balance ability and [lower](app:ds:lower) [limbs](app:ds:limbs) proprioception will be assessed at Rehabilitation Hospital Affiliated to FJTCM by three experienced [rehabilitation](app:ds:rehabilitation) [therapist](app:ds:therapist)s who do not involve in this study. The physical fitness test, [cardio-pulmonary](app:ds:cardio-pulmonary) [function](app:ds:function), flexibility, vital capacity, and weight will be conducted at campus gymnasium by the physical education teachers. The outcome assessors of this trial will be in charge of the assessment of relevant psychology scales including self-efficiency, attention, stress self-esteem, and quality of sleep.

**Primary outcome measures**

1. Balance ability

It will be tested by standing with eyes open for 30 seconds and standing with eyes closed for 30 seconds via Pro-kin system(Machine type: produce by *Italy Tecnobody. S.R.L company, model PK254P*)

2. Lower [limbs](app:ds:limbs) proprioception: both left and right legs will be tested via Pro-kin system (*Machine type: produce by Italy Tecnobody. S.R.L company, model PK254P*).

3. Flexibility: will be tested with Sit and Reach flexibility test equipment (Machine type: *Beijing ZhongTi Tongfang Co., Ltd., model CSTF-TQ-5000*).

4. Self-efficiency: *The* *Self-Regulatory Self-Efficacy Scale* will be used to test self-efficiency.

5. Psychological symptom score: will be assessed by using *SCL-90 scale* .

6. Attention span: will be assessed with *Schulte grid (8*8) scale.*
7. Stress: will be measured with *Chinese Perceived Stress Scale* .

**Secondary outcomes measures**

1. [cardio-pulmonary](app:ds:cardio-pulmonary) [function](app:ds:function): will be evaluated indirectly by step test, vital capacity, blood pressure and rest heart rate. Step testing：step test will be conducted by Electronic step test instrument（stairs with 30 [centimeter](app:ds:centimeter)s of step height will be used for males, and 25 [centimeter](app:ds:centimeter)s of step height will be used to females）(Machine type: *Beijing ZhongTi Tongfang Co., Ltd., model CSTF-TZ-5000*). Vital Capacity: will be tested by electronic vital capacity instrument (Machine type: *Beijing ZhongTi Tongfang Co., Ltd., model CSTF-FH-5000*); blood pressure and rest heart rate will be tested by electric sphygmomanometers produced by the *Omron Corporation, China* (product type: *HEM-746C*).

2. Self-esteem: will be assessed with self-esteem scale.

3. Mood and mindfulness: will be measured with *Profile of Mood States (POMS)*.
4. Quality of life: will be tested with *WHOQOL-BREF scale*.

5. Sleep quality: will be measured by using the *Pittsburgh Sleep Quality Index (PSQI)*.

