**Methods/Design**

**Study design**

The study about the effectiveness of TCC on physical health and psychosocial well-being of college students is designed as a randomized, parallel controlled, assessor and statistician single-blinded trial. The allocation of participants will be equal (1:1) to the TCC exercise group (intervention group) and the control group. All assessment will be conducted by the blinded assessors at Fujian University of Traditional Chinese Medicine Affiliated Rehabilitation Hospital, and the gymnasium of FJTCM. The TCC exercise will be conducted at the gymnasium of FuJian University of TCM, and instructed by two qualified coaches. The entire trial program is illustrated in Figure 1.

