**Randomization and allocation concealment**

Participants will be randomly allocated to the TCC training group or the control group. Randomization will be performed at post-baseline assessment. The randomization list will be generated via Statistical Analysis System (SAS, version 9.1) by an independent non-investigator who works in Center for EBM of Academy of Integrative Medicine FuJian China. The allocation sequence will be concealed through a password access files which will be taken care of by the project manager. The eligible participants will be informed the allocated result by the project manager after post-baseline assessment.

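### Sex sets the step-test load but is named in neither the randomisation nor the default comparison; naming it would be a small, cheap gain in precision for two secondary measures

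*Protocol*

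**What the plan says.** Protocol, Secondary outcomes measures, item 1: cardio-pulmonary function "will be evaluated indirectly by step test, vital capacity, blood pressure and rest heart rate". For the step test, a height of 30 cm "of step height will be used for males, and 25" cm "of step height will be used to females". The inclusion criteria do not restrict sex, so both loads will be in use.

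Protocol, Randomization and allocation concealment: "The randomization list will be generated via Statistical Analysis System (SAS, version 9.1) by an independent non-investigator". No stratification factor is named. Allocation follows the baseline assessment, and Table 1 places both in weeks -2 to -1.

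Protocol, Statistical analyses plan: "For the variables with a normal distribution, statistical comparisons between the groups will be made by using a" *t* test, with the Mann-Whitney U test for non-normal variables. Then: "A general linear model or Logistic regression model will be applied to adjust the confounding influence if necessary". Sex is not mentioned, no covariate is named, and nothing says when adjustment becomes necessary. The section also does not say whether final values or changes from baseline are compared.

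**The concern.** The protocol itself treats sex as relevant to the step test, since it sets a different load for each sex. Sex is known for every student before allocation. Yet the default comparison puts men and women in one two-group test with no term for sex. If the sexes differ in step-test score, that difference counts as unexplained variation and widens the interval for the effect of Tai Chi. The same holds for vital capacity if it differs by sex.

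The conditional model does not settle this. Its stated purpose is to deal with confounding, whereas the loss here is one of precision. Because neither the covariate nor the trigger is fixed, the choice could also be made after the data are seen. At stake is the precision of two secondary measures, not the validity of the trial.

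**Working it through.** The protocol gives no figure on this point: no sex mix, no sex-specific mean or SD, and no definition of the step-test score. Its sample size rests on balance and is not tested here. From the document I take 103 students per group recruited and 93 per group before the dropout allowance. Everything else is an assumption, shown as a range: *g* is the gap between the sexes in within-sex SDs, *p* is the share of one sex, and *r* is the within-sex correlation between baseline and follow-up.

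**1. Unadjusted comparison.** With within-sex variance 1, the pooled variance is 1 + p(1-p)g². Power is for an effect that would have 90% power with 93 per arm if sex were adjusted for, two-sided 5%: Φ(3.24/√variance - 1.96).

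| g | variance, 50:50 | power, 50:50 | variance, 70:30 | power, 70:30 |
|---|---|---|---|---|
| 0 | 1.00 | 90% | 1.00 | 90% |
| 0.5 | 1.06 | 88.2% | 1.05 | 88.5% |
| 1 | 1.25 | 82.6% | 1.21 | 83.8% |
| 2 | 2.00 | 63.0% | 1.84 | 66.6% |

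The 50:50 mix is the worst case, because p(1-p) is largest there.

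**2. Chance sex imbalance is the same loss.** With 103 per arm and no stratification, the 95% range for the difference in the proportion of men is ±1.96 × √(2 × 0.25/103) = ±0.137 at 50:50, and ±1.96 × √(2 × 0.21/103) = ±0.125 at 70:30. At g = 1 the 50:50 imbalance would move the arm difference by 0.14 SD. The variance of that shift is g² × 2p(1-p)/103, and the extra variance of the arm difference from pooling is p(1-p)g² × 2/103. These are identical. At g = 1 and 50:50: 2/103 + 0.5/103 = 0.0194 + 0.0049 = 0.0243, which is 1.25 × 0.0194. The shift is already inside the 25% and must not be added to it.

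**3. With the baseline value in the model.** Assume a 50:50 mix, the same gap at both visits and equal within-sex SDs. Put V = 1 + g²/4. The residual variance with baseline only is V - (r + g²/4)²/V; with baseline and sex it is 1 - r².

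| g | r | baseline only | baseline and sex | saving |
|---|---|---|---|---|
| 1 | 0.5 | 1.25 - 0.75²/1.25 = 0.800 | 0.75 | 6.2% |
| 1 | 0.7 | 1.25 - 0.95²/1.25 = 0.528 | 0.51 | 3.4% |
| 2 | 0.5 | 2 - 1.5²/2 = 0.875 | 0.75 | 14.3% |
| 2 | 0.7 | 2 - 1.7²/2 = 0.555 | 0.51 | 8.1% |

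Most of the gain therefore comes from the baseline value; sex adds a little more.

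**4. If changes from baseline were compared.** A constant gap cancels, and the variance is 2(1-r): 1.00 at r = 0.5 and 0.60 at r = 0.7. That is free of the sex gap but still above 0.75 and 0.51.

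**The case against.** The strongest reply is that nothing in the protocol is wrong here. Step height depends on sex and not on arm, so each sex takes the same test in both arms, and randomisation balances sex in expectation. The analysis section does allow a general linear model, and sex could enter it. A separate SAP, not available here, may name the covariates. The measures concerned are secondary, and the gap between the sexes is unknown.

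Most of this stands, and it rules out several stronger readings that a reader might infer:

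- *The pooled step-test comparison is biased or invalid.* It is not, for the reason just given; only precision is lost.
- *Sex is excluded from the analysis.* The conditional model leaves room for it. The fair complaint is that neither the covariate nor the trigger is fixed.
- *The list is known to be unstratified.* The section is silent on strata; it does not rule them out.
- *The two step heights create the gap.* No scores are given, and a lower step for women could as well narrow a gap as widen it.
- *Sex belongs in the model for every physical outcome.* The document gives no sign of a sex difference in balance, proprioception or flexibility, so there is no basis for extending the point to these primary outcomes.

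What the reply does not remove is that the protocol's own analysis section fixes the unadjusted test as the default. A better comparison is available from data the trial already collects.

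**Conclusion.** The point holds as a minor efficiency improvement. As written, the default test for the step test and vital capacity ignores sex, and any sex gap goes into the error term. The cost runs from nothing (no gap) through 6% extra variance (0.5 SD) and 25% (1 SD) to 100% (2 SD) with a 50:50 mix, or 21% and 84% at 1 and 2 SD with a 70:30 mix. All of these figures rest on assumed gaps and mixes.

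The 100% figure, equivalent to losing half the sample, needs the largest gap considered, an even mix and no use of the baseline value, so it should not be read as the expected loss. Against a model that already includes baseline, naming sex is worth about 3-6% of the variance at 1 SD and 8-14% at 2 SD, for r between 0.5 and 0.7. The sample size, which rests on balance, is not affected.

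**What to change.** In the Statistical analyses plan section, state that the arms will be compared on the step test and vital capacity with a linear model containing arm, the outcome's own baseline value and sex, in place of the unadjusted two-group test, and that this is fixed in advance and not conditional on necessity. The step heights themselves need no change for this purpose.

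If allocation has not yet taken place, the independent person who generates the SAS list could also stratify it by sex. Sex is known before allocation, so this is feasible, but it is optional: the model term alone recovers most of the benefit, and if allocation is done it is the only part still open.

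The cost is one or two model terms and, if stratification is chosen, a slightly longer list program. No further data, visits or students are needed.
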